**Primary Outcome**

Proportion of service users admitted or otherwise subsequently detained under an order of the Mental Health Act during the follow-up period.

Sample Size

**The primary outcome is reduction in the proportion of service users admitted or detained under a Mental Health Act section at least once, obtained from records. In the pilot trial based in London 26% were compulsorily admitted over 15 months, equivalent to 30% over 18 months. Routine data for inner city wards in Birmingham and Manchester show a very similar proportion, on average. Assuming that a clinically important reduction would be to at least halve the proportion, i.e. a reduction in absolute terms by 15% to 15%, 90% power using a double-sided test with alpha=0.05 would require 174 in each arm.**

**For the ethnic subgroup analysis where the baseline compulsory admission rate is likely to be higher, an achieved subsample of 91 per arm would give 80% power to detect a difference from 40% to 20% Given the percentages of service users likely to be black at each site (from recent actual MHA use data), 90 are likely to be found with a sample of 270 per arm, and the minimum achieved would be about 80 with a slight reduction in power.**

**Loss to follow-up is likely to be about 15% for the interview data so this sample size (270) would reduce to an effective 229 per arm, which would allow standardised effect sizes of 0.3 for the secondary outcomes to be detectable with 90% power. The total to be recruited would therefore be 540, or 180 per centre.**

**Measures**

B=Baseline, FU Follow-up at 18 months post baseline

**Colleagues with as special interest in the outcome scales are noted below in case of queries regarding scoring or interpretation. This is a preliminary suggestion and subject to change – please contact SF or ML if you prefer not to be the ‘expert’ for the particular scale or would rather take on another (or no) scale.** **We need someone to take an interest in the Engagement and Acceptance scale**

| **Primary/secondary outcomes** | **Standardised measure** | **Source** | **Time** |
| --- | --- | --- | --- |
| MHA use (primary) | Routine hospital datasets | Admin. Records + Patient Information Records using Admissions Proforma* | B FU |
| Informal admissions | As above | As above | B FU |
| Recovery Style  (MB) | Recovery Style Questionnaire | Self-report** | B FU |
| Perceived coercion  (GS) | Treatment Experience Survey (Community) | Self-report (based on MacArthur AES) ** | B FU |
| Engagement with care  (?) | Engagement and Acceptance Scale | Staff-rated | B FU |
| Therapeutic relationship  (JS) | Working Alliance Inventory | Self-report**  and Staff-rated | B FU |

*To be collected for all patients including dropouts (refusals or uncontactable) unless patient specifically requests otherwise.

** Interviewer helps in cases of literacy problems only

| **Other outcomes*** | **Standardised measure** | **Source** | **Time** |
| --- | --- | --- | --- |
| Functioning  (SF) | Global Assessment of Function (GAF) | Rater | B FU |
|  |  |  |  |
| Involuntary transport to hospital  under the MHA | Admissions Proforma | Case notes | B FU |
| Police involvement in admission | Admissions Proforma | Case notes | B FU |
| Incidents of violence and sef-harm  (MB?) | COMMAND questionnaire | Interview | B FU |
| Criminal justice system involvement  (SB/BB) | Crimson AD-SUS | Interview | B FU |

Is GAF an outcome as such or is it a predictor?

| **Socio-demographic data*** | **Standardised measure** | **Source** | **Time** |
| --- | --- | --- | --- |
| OPCRIT diagnosis  (MHRN CSO at each centre) | OPCRIT | Case notes | Eligibility (prebaseline) |
| Centre |  |  | B |
| Gender | Crimson Sociodemographics | Interview | B |
| Ethnic group (W, BA, BC, other) | Crimson Sociodemographics | Interview | B |
| Age | Crimson Sociodemographics | Interview | B |
| Clinical diagnosis  (SF) | Crimson Sociodemographics | Case notes (text -codes to be decided) | B |
| Educational level | Crimson Sociodemographics | Categories to be combined | B FU |
| Marital Status | Crimson Sociodemographics | Categories to be combined | B FU |
| Accommodation (lives with, type) | Crimson AD-SUS | Categories to be combined | B FU |
| Occupational classification (ONS) | Crimson AD-SUS | Categories to be combined | B FU |
| Employment | Crimson AD-SUS | Categories to be combined | B FU |

* Key variables only included here

**Further data**

- Fidelity and Quality Rating of Plan Scores

Fidelity score A (preparatory meeting) and B (joint crisis planning meeting), rated from audio recordings by KS and CH.

Currently 10 per centre. But if scores fro clinical and non clinical facilitators to be compared then much larger sample required (suggest all) and interrater reliability needs to be considered.

Quality Rating of Plan – to be finalised by ?

- Activation of Plan

Whether or not plan actually activated and/or paid attention to? How to collect without affecting intervention or blinding, resource issues, type of data that is available, consistency across centres.

- Care Coordinators

Data to be collected on care coordinators will be gender, ethnicity, age, professional qualification (OT, CPN, psychologist, other), length of relationship with participant, length of practice, first language (NB patient’s first language not collected – collect at followup?).

**Data Management**

The package MACRO (via the IOP CTU) will be used for data input. Interim reports on numbers recruited (including ethnic breakdown by arm) and random data quality checks will be made (all primary outcome and 10% of others to be checked by SF) every quarter.

**Type of analyses**

An intention-to-treat analysis will be applied in the first instance (i.e. analysing all available data from service users in their groups as randomised), using double-sided critical values at 0.05.

No adjustment for multiple testing but secondary analyses will be treated as exploratory.

There will be no interim analyses. All hypotheses-related analyses will be conducted only at the end of the follow-up period.

**Statistical Methods**

The principal analysis will compare the primary and secondary outcome measures at 18 months, combined over centres. The proportions admitted to hospital under a section at follow up will be compared between randomisation groups using logistic regression controlling for centre and ethnic group.

Other (continuous) outcomes such as therapeutic alliance and engagement with mental health services will be analysed using analysis of covariance controlling for baseline (pre-intervention) measures, ethnic group and centre. Short scales will be analysed using ordered logistic regression, otherwise linear regression. Bed-days and other very skewed data will be analysed using bootstrapping to obtain confidence intervals and p-values.

Number of admissions (informal and under MHA) will be analysed using Poisson regression, and time to first admission using survival analysis

SPSS version 12 and Stata version 10 will be used for the analyses.

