**8.2. Analysis plan**

The principal analysis of effectiveness will compare the primary and secondary outcome measures at 18 months, combined over centres. The proportions admitted to hospital under a section at follow up will be compared between randomisation groups using logistic regression controlling for centre. Other (continuous) outcomes such as therapeutic alliance and engagement with mental health services will be analysed using analysis of covariance controlling for baseline (pre-intervention) measures and centre. Number of admissions will be analysed using Poisson regression, and time to first admission using survival analysis. Bed-days and other very skewed data will be analysed using bootstrapping to obtain confidence intervals and p-values70. Short scales will be analysed using ordered logistic regression. An intention-to-treat analysis will be applied in the first instance (i.e. analysing all available data from service users as randomised). Time trends in measures available at baseline and two time points will be analysed using methods for longitudinal data such as random effects regression. Sensitivity analyses will be performed to assess the influence of loss to follow-up and refusals, including imputation of missing baseline values from the within-centre means; multiple imputation of follow up values (where feasible from other variables) and CACE analyses65. (Full analysis plan is in Appendix 4)

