**Planned Subgroup Analyses**

- Ethnic group (Whites, the combined Black subgroup, which consists of black Caribbeans and black Africans, and others).

The study is not specifically powered to detect interactions between ethnic group and treatment arm. However the black group is considered to be of interest in its own right and therefore a parallel analysis will be applied to this subgroup. The purpose would not be to identify differences compared to the white group but to separately establish the effectiveness of the intervention for black clients.

- Facilitators: the scope for analysing their individual effect will be limited (although see above under fidelity: the fidelity score for particular facilitator/user meetings will be included in further exploratory analyses of intervention effects and also to compare clinical facilitators with their nonclinical backups.
- Care coordinators: variation contributed by care coordinators will be taken account of by including them as random effects in regression models, in which the effect of their characteristics will also be assessed.

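### Number of admissions is to be analysed by Poisson regression with no stated allowance for overdispersion, so its intervals and p-values may be too optimistic

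*Protocol*

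**What the plan says.** Section 8.2 states: "Number of admissions will be analysed using Poisson regression, and time to first admission using survival analysis". Statistical Methods in Appendix 5 repeats the choice and makes clear that the count covers both kinds of admission: "Number of admissions (informal and under MHA) will be analysed using Poisson regression". Neither place names a variance estimator, a dispersion parameter, an alternative count model or an exposure term.

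Three other statements bear on the point:

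- Skewed outcomes have a separate rule in the same part of Appendix 5: "Bed-days and other very skewed data will be analysed using bootstrapping to obtain confidence intervals and p-values". Admissions are not named there and have their own sentence.
- Tests are run "using double-sided critical values at 0.05", and on multiplicity the plan says: "No adjustment for multiple testing but secondary analyses will be treated as exploratory".
- Under Planned Subgroup Analyses, "variation contributed by care coordinators will be taken account of by including them as random effects in regression models". The models meant are not named.

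**The concern.** Poisson regression takes the variance of the count to equal its mean once the covariates are in the model. Admission risk in this trial is likely to vary a good deal between patients. Section 5.2 requires only one in-patient admission in the previous two years, so people with a single admission enter alongside people who relapse often. It also admits assertive outreach, early intervention and community forensic caseloads, and all psychotic illness including bipolar disorder. Centre and ethnic group cannot account for most of that variation. If it is present and the model's default variance is used, the interval for the admission rate ratio is too narrow and its p-value too small.

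At stake is the reliability of one reported comparison. A nominally significant difference in number of admissions could be read as support for the intervention when the evidence is weaker than it appears.

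**Working it through.** **The plan's own figures.** The protocol gives no mean, variance, power or error rate for the number of admissions. The nearest stated figures belong to the primary outcome.

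- The control rate, "26% were compulsorily admitted over 15 months, equivalent to 30% over 18 months", is consistent with a constant hazard: 1 − (1 − 0.26)^(18/15) = 0.303.
- For the sample size, "90% power using a double-sided test with alpha=0.05 would require 174 in each arm": with 30% against 15%, the pooled-variance formula gives [1.960 × √(2 × 0.225 × 0.775) + 1.282 × √(0.30 × 0.70 + 0.15 × 0.85)]² / 0.15² = 160.8, or 161 per arm. The continuity correction raises this to 174, so the stated figure is reproduced.

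These figures concern a proportion and do not depend on the count model.

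**Effect of overdispersion on the Poisson test.** Let φ be the variance/mean ratio after covariates. This is an assumption, because the protocol gives no value. The Poisson standard error is 1/√φ of the true one, so under the null the test statistic has standard deviation √φ. At a nominal two-sided 0.05:

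actual error = 2 × [1 − Φ(1.96/√φ)]

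| φ (assumed) | Reported SE / true SE | Interval too narrow by factor | 1.96/√φ | Actual error |
|---|---|---|---|---|
| 1 | 1.00 | 1.00 | 1.960 | 5.0% |
| 1.25 | 0.89 | 1.12 | 1.753 | 8.0% |
| 1.5 | 0.82 | 1.22 | 1.600 | 11.0% |
| 2 | 0.71 | 1.41 | 1.386 | 16.6% |
| 3 | 0.58 | 1.73 | 1.132 | 25.8% |
| 4 | 0.50 | 2.00 | 0.980 | 32.7% |

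**Check by simulation.** Negative binomial counts were drawn under the null with 270 per arm and 20,000 replicates per setting, and the log rate ratio was tested without covariates. With variance μ + aμ², φ = 1 + aμ. The mean μ was chosen so that a set proportion p had at least one admission, which gives φ = (1 − p)^(−a). The dispersion a is assumed. The value p = 30% is the protocol's figure for compulsory admission. The value p = 50% is an assumption for any admission, since the outcome also counts informal ones.

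| a (assumed) | φ at p = 30% | Poisson error | φ at p = 50% | Poisson error |
|---|---|---|---|---|
| 0 | 1.00 | 0.048 | 1.00 | 0.048 |
| 0.5 | 1.20 | 0.075 | 1.41 | 0.102 |
| 1 | 1.43 | 0.100 | 2.00 | 0.165 |
| 2 | 2.04 | 0.170 | 4.00 | 0.324 |
| 3 | 2.92 | 0.251 | 8.00 | 0.493 |

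With a robust (sandwich) variance on the same data, the error lay between 0.049 and 0.055 in all ten settings, including those with no overdispersion.

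**The case against.** The strongest reply is that the plan names a model family and no variance estimator. Poisson regression with robust standard errors is still Poisson regression, and such detail is often left to a later analysis plan. Appendix 5 is marked as a second draft and has open items. This fairly limits the point: the text omits a safeguard and does not rule one out. It does not dispose of it. Section 8.2 calls the appended plan the full one, and that plan is specific enough to assign bootstrapping to skewed data while giving admissions a different method.

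A second reply is that care-coordinator random effects would take up the extra variation. They could take up part of it, and perhaps most of it if coordinators had one participant each. But the plan does not say that they enter this model, and in general they do not absorb differences between patients of the same coordinator.

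A third is that secondary analyses are declared exploratory. That lowers the consequence but does not make the interval valid.

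Two stronger readings are tempting. A reader might infer that the analysis will produce too many false positives. The protocol does not show this: the proportion with at least one compulsory admission says nothing about how many people have several, and at φ = 1 there is no inflation. A reader might also infer that the primary claim or the cost result is undermined. Neither is. The primary outcome is a proportion analysed by logistic regression, and section 8.3 bootstraps the cost difference. Number of admissions is not in the hypotheses of section 4 or the secondary list of section 7.1.

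A missing time-at-risk term is a lesser matter. Admission data come from records, for dropouts too unless the participant objects, so exposure should differ mainly through death or loss of record coverage.

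**Conclusion.** The point holds in conditional form. The plan fixes Poisson regression for number of admissions and does not say how overdispersion will be handled. If the variance/mean ratio after covariates is 1.5, 2 or 3, a nominal 5% test has an actual error of about 11%, 17% or 26%. These figures assume that the default Poisson variance is used, and the ratios themselves are assumptions. Overdispersion is the likely case given the eligibility criteria, but its size cannot be taken from the protocol. The reach is confined to one secondary, exploratory count outcome.

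**What to change.** In section 8.2 and in Statistical Methods of Appendix 5, state that number of admissions will be analysed by negative binomial regression, or by Poisson regression with robust standard errors or the bootstrap already planned for skewed data. Name the same covariates as the primary model. Appendix 5 lists centre and ethnic group for that model and section 8.2 lists centre only, so the two should agree first. Add log time at risk as an offset where follow-up is truncated by death or loss of record coverage.

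The cost is one line in each place. With no overdispersion, almost nothing is lost: the simulated error of the robust test was about 5% there too. Where overdispersion exists, intervals widen by about √φ, for example by a factor of 1.41 at φ = 2. The sample size and the primary analysis need no change.

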**Missing Data**

Some outcome data (in particular the primary outcome) will be obtained from staff, case notes, and administrative sources, and even for service users lost to follow-up.

Sensitivity analyses will be performed to assess the influence of loss to follow-up and refusals, including imputation of missing baseline values from the within-centre means; multiple imputation of follow up values (where feasible from other variables) and controlling for any baseline variables that are related to missing outcomes in the analysis.

- The content of the facilitators’ meetings will be assessed using the specially designed fidelity scale.
- The content of the Care Programme Approach of randomly selected cases in both arms will be tested at 9 months.

Number to be decided – probably on the basis of an equivalence test on some total score depending on how this is measured (scale to be developed).

- Research raters’ ‘best guesses’ of trial arm will be assessed to test whether their blindness is maintained*.*

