# Protocol Amendments and Approvals

The following changes and approvals have been made to the protocol.

| ***Version Number*** | ***Date*** | ***Submitted/shown to*** | ***Amendments*** | ***Section*** |
| --- | --- | --- | --- | --- |
| 1 | 29 September 2006 | MRC grants office |  |  |
| 2 | 23 October 2007 | n/a | Add assessment of CPA review | Control intervention |
| 3 | 31 October 2007 | Approved by ethics | Focus group timing and overall sample numbers  Revised numbering of references | Proposed trial  Reference |
| 4 | 6 May 2008 | Approved by ethics 06 May 2008 | Add CC socio demogs and JCP experience study | Proposed trial |
| 5 | 4 June 2008 | Ethics committee 23 July 2008 | Reformat protocol for submission to Lancet. Content not changed. Addition of: ‘General information’ section; protocol amendment and approvals section; |  |
| 6 | 22 September 2008 | Ethics committee | - Addition of Service Engagement Scale (SES) - Update study team lists and analysis plan | - 7 – Assessments - Appendices |
| 7 | 21 January 2009 |  | - addition of recruitment projections/plan chart - detail of length of recruitment period - ‘detained or treated’ added to the description of primary outcome - Change of ‘societal’ to ‘broad’ perspective in description of economic analysis - Revised Enhanced CPA criterion following new guidelines | - Appendix 3 - Section 5 - Section 4 - Section 7.3 |
| 8 | 20 April 2009 |  | - clarification of eligibility criteria ‘adults (aged 16 and above)..’ | Eligibility criteria |
| 9 | 23 September 2009 | Ethics committee  30/11/09 | - Trial end date altered post extension from MRC - update TSC membership and DMEC membership - update methodology for CPA audit - addition of psychiatrist interviews to qualitative studies | General Information, appendix 3 and section 10  6. The intervention  7.2. Qualitative studies |
| 10 | 22 February 2011 | Ethics committee 31/3/2011 | - collection of demographic data of refusals - contacting refusers of intervention to clarify further involvement | 5.1 and 7.1 |
| **11** | **24 May 2011** | **Awaiting approval** | **- adding individual interviews for sectioned intervention participants.** | **7.2** |
|  |  |  |  |  |
|  |  |  |  |  |
|  |  |  |  |  |
|  |  |  |  |  |
|  |  |  |  |  |

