**Secondary:**

1. Cost as measured by the Adult Service-Use Schedule (see section 3.11)
2. Perceived coercion (Admission Experience Inventory)48
3. Engagement with mental health services (Engagement and Acceptance Scale49 and Service Engagement Scale 60
4. Therapeutic relationship for service users and staff (Working Alliance Inventory)50

In addition socio-demographic data will be collected at baseline, and social and functional clinical descriptors (baseline and follow-up) will be gathered along with the Global Assessment of Function51. We shall also record: involuntary transport to hospital under the MHA, police involvement in admission, incidents of violence, incidents of self harm, and criminal justice system involvement. In addition we shall conduct systematic analyses of the content of these JCPs in terms of treatment preferences, instructions, information, and consent or refusal of interventions. Ethnicity will be described using ONS categories as they have been thoroughly tested and are known to be acceptable to the majority of the population52. Additionally, socio-demographic data and length of practice data will be collected for care co-ordinators.

To ensure the accurate reporting of the representativeness of the trial sample, we will collect basic demographic data (age, gender, diagnosis, ethnicity and last hospital admission) on those who refused to participate in the trial.

At follow-up we will contact all participants who originally participated in the trial. Intervention participants who refused to complete a Joint Crisis Plan, will be contacted via a letter to clarify their wishes for any further involvement in the trial.

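### The main ANCOVA drops participants who have an 18-month score but no baseline, because filling missing baselines is only a sensitivity analysis; the Service Engagement Scale is the measure most exposed

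*Protocol*

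**What the plan says.** **Main model.** Protocol section 8.2 specifies "analysis of covariance controlling for baseline (pre-intervention) measures and centre" for continuous outcomes such as engagement. Appendix 5 (Analysis Plan), under Statistical Methods, adds ethnic group: "analysis of covariance controlling for baseline (pre-intervention) measures, ethnic group and centre".

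**Missing baselines.** Section 8.2 deals with these in one place: "Sensitivity analyses will be performed to assess the influence of loss to follow-up and refusals, including imputation of missing baseline values". Appendix 5, under Missing Data, repeats this and names the method, "including imputation of missing baseline values from the within-centre means". Neither passage gives the main model a rule for a missing baseline.

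**Analysis set.** Appendix 5, under Type of analyses, defines the first analysis as intention to treat, using whatever data are available on participants in the arm to which they were randomised. Section 8.2 says the same.

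**Engagement measures.** Section 7.1 lists two scales: "Engagement with mental health services (Engagement and Acceptance Scale49 and Service Engagement Scale 60". The outcome table in section 7.2 gives both as staff-reported at baseline and at 18 months. The amendment table in section 2 records "Addition of Service Engagement Scale (SES") at version 6, dated 22 September 2008. The appended plan is dated 26 August 2008, and its measures table has only the Engagement and Acceptance Scale for engagement.

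**The concern.** A regression on a baseline covariate cannot use a record in which that covariate is missing unless the plan says how to fill it. Here the plan does name a way to fill it, but reserves it for sensitivity analyses whose stated purpose is to examine loss to follow-up and refusals. Those are problems of missing outcomes. A baseline that is missing because a scale was introduced late, or because a form was not returned, is a different problem: the outcome is observed, and the participant is discarded for want of a pre-randomisation covariate.

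The Service Engagement Scale is the clearest candidate. Anyone recruited before it came into use would have no baseline on it but could still have an 18-month score.

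Engagement is a stated secondary hypothesis, and section 8.1 makes a power claim for the secondary outcomes. At stake are precision on that scale and consistency with the plan's own intention-to-treat rule.

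**Working it through.** **Inputs from the protocol**
- 270 per arm, 15% loss for interview data, 229 per arm effective, effect 0.3 SD, 90% power (section 8.1).
- Two-sided 5% level (Appendix 5, Type of analyses); equal allocation (section 5.1).
- 540 participants in total (section 8.1), recruited over 18 months (section 5).

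**Inputs that are assumptions, because the protocol does not give them**
- f, the share of participants with an 18-month score but no baseline.
- r, the correlation between baseline and 18-month score.

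**1. Reproduce the plan's figure.** 270 × 0.85 = 229.5. With n per arm and residual SD σ, power ≈ Φ(0.3 / (σ√(2/n)) − 1.96). For n = 229 and σ = 1, 0.3/√(2/229) = 3.21, so power = Φ(1.25) = 89.4%. The n for exactly 90% is 2(1.960 + 1.282)²/0.3² = 233.5, or 234. The plan's 229 at 90% is reproduced to rounding.

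**2. Drop those without a baseline (main model as written).** n = 229(1 − f), σ² = 1 − r².

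**3. Keep them, with the baseline set to the centre mean.** n = 229. Filled cases get no covariate adjustment, so the average residual variance is σ² = (1 − f)(1 − r²) + f. At r = 0.5 this is 0.775 for f = 10% and 0.80 for f = 20%.

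| f | n per arm if dropped | Power, dropped, r = 0 | Power, kept, r = 0 | Power, dropped, r = 0.5 | Power, kept, r = 0.5 |
|---|---|---|---|---|---|
| 0% | 229 | 89.4% | 89.4% | 96.0% | 96.0% |
| 10% | 206 | 86.1% | 89.4% | 94.0% | 95.4% |
| 20% | 183 | 81.9% | 89.4% | 91.2% | 94.8% |

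**4. What f might be for the Service Engagement Scale.** If entry was uniform over 18 months and began m months before the scale was in use, f = m/18:
- m = 0: f = 0, no loss from this cause.
- m = 1: 540/18 = 30 participants, 216 per arm, 87.7% power at r = 0.
- m = 3: 90 participants, 191 per arm, 83.4% at r = 0. At r = 0.5 it is about 92% if dropped and 95% if kept.

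The protocol does not fix m.

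**5. Does filling distort the comparison?** The filled value depends on centre only. If the baseline was due before randomisation and the mean is taken over both arms, it carries no information about allocation, so the treatment comparison is not biased by it.

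**The case against.** **No one need have been enrolled before the scale was in use.** This stands. The only hint is a note in the August 2008 plan that a patient item was "first language not collected – collect at followup". It shows that a form had been designed, not that anyone had completed it. The same plan speaks of recruitment in the future tense, and version 7 (January 2009) was still adding recruitment projections. A reader might infer that early entrants certainly lack a baseline score; the documents do not support that.

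**Only one of two engagement scales is touched.** This also stands. The Engagement and Acceptance Scale is in the August 2008 plan. A reader might infer that the whole engagement result is confined to later entrants. The amendment gives no ground for that.

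**The power loss depends on favourable choices.** Partly right. The sub-90% figures need r = 0, a pessimistic value for a model chosen to exploit baseline. The 229 reflects interview loss, whereas the scale is staff-rated and some outcome data are to come from staff even for participants lost to interview. If all 270 per arm had an 18-month rating, losing three months' entrants would leave 270 × 15/18 = 225, close to the planned 229.

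**Staff forms.** A reader might also infer widespread gaps because the blinding appendix names only participants and electronic systems as sources of pre-randomisation baseline data. That appendix asks for all baseline data, so the gaps are conjecture. Moreover, if staff forms could come back after randomisation, their absence might depend on arm and the no-bias argument would weaken. The fix is limited accordingly.

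**This belongs in a later SAP.** Silence would. But section 8.2 calls the appendix the full analysis plan, and both texts place baseline imputation explicitly among the sensitivity analyses. That is a stated choice, and a better one is available at almost no cost.

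**Conclusion.** The point holds as a matter of how the main model is specified. It discards observed 18-month scores when the baseline is missing, at odds with the plan's own rule on available data, while the method that would keep them is relegated to a sensitivity analysis. It applies to any continuous secondary outcome with a missing baseline.

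The size is uncertain and could be nil. On the stated assumptions, a 10% to 20% loss costs about 3 to 8 percentage points of power at r = 0 (89.4% to 86.1% or 81.9%). At r = 0.5 it costs about 1 to 4 points relative to keeping everyone, with power still above 90%. A baseline missing only because of entry date is unrelated to arm, so the harm is to precision rather than validity. The primary outcome is unaffected, and Appendix 5 treats secondary analyses as exploratory. This is a modest, worthwhile correction and not a threat to the trial's conclusions.

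**What to change.** In section 8.2 and in Appendix 5 (Statistical Methods and Missing Data):

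1. State that the main ANCOVA includes every participant with an 18-month value. Replace a missing baseline by the mean for that centre computed over both arms together, optionally with a missing-baseline indicator.
2. Restrict this to baseline measures that were due before randomisation.
3. Make the complete-baseline ANCOVA the sensitivity analysis.
4. Add the Service Engagement Scale to the measures table in Appendix 5, and report how many participants have an 18-month score but no baseline.

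The cost is wording only: no new data or visits, and the method is already named in the plan. The one statistical price is slightly less covariate adjustment for the filled cases, which the table above already includes.
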